## 5. Toxicity

No toxicity is expected in administration of vitamins and minerals given at 1-3 times RDA levels. The proposed levels of micronutrients are shown in Tables 5 and 6 below

Table 5. Proposed Dosages, Dysplasia Trial

| Nutrient                           | Dose | %RDA |
|-------------------------------------------|-------------|-------------|
| Vitamin A (as acetate)                    | 10,000 IU   | 200         |
| Beta-carotene                             | 25 mg       | -           |
| Riboflavin                                | 5.2 mg      | 300         |
| Niacin (as niacinamide)                   | 40 mg       | 200         |
| Vitamin C (as ascorbic acid)              | 180 mg      | 300         |
| Vitamin E (as dl-alpha tocopherylacetate) | 20 mg       | 200         |
| Selenium (as sodium selenate)             | 50 mcg      | -           |
| Zinc (as zinc sulfate)                    | 45 mg       | 300         |
| Molybdenum (as sodium molybdate)          | 30 mcg      | -           |

Table 6. Proposed Dosages, General Population Trial

| Nutrient                           | Dose | %RDA |
|-------------------------------------------|-------------|-------------|
| Vitamin A (as acetate)                    | 5000 IU     | 100         |
| Beta-carotene                             | 25 mg       | -           |
| Riboflavin                                | 3.2 mg      | 200         |
| Niacin (as niacinamide)                   | 40 mg       | 200         |
| Vitamin C (as ascorbic acid)              | 120 mg      | 200         |
| Vitamin E (as dl-alpha tocopherylacetate) | 20 mg       | 200         |
| Selenium (as sodium selenate)             | 50 mcg      | -           |
| Zinc (as zinc sulfate)                    | 22.5 mg     | 150         |
| Molybdenum (as sodium molybdate)          | 30 mcg      | -           |

These doses are well within the level of intake in the American population as a whole, for which no long-term toxicity has been reported.

The water-soluble vitamins are rapidly excreted with essentially no short-or long-term toxicity reported.

The fat-soluble vitamins are stored in the body for a longer time and have the potential for toxicity. However, no vitamin A toxicity has been reported for long-term intakes of less than 50,000 IU or 15,000 retinol equivalents [1 R.E. of retinol = 3.33 I.U. and 1 R.E. of Carotene = 6 mcg.] daily.(28) Beta-carotene has no known serious side effects although, depending on body size and dietary carotene intake, it may cause reversible yellowing of the skin. With the possible exception of muscle pain, vitamin E has no documented toxicity, even in doses in excess of 400 IU/day. (29)

Selenium has been reported to cause toxicity in humans but only when daily intake exceeds 3 mg (60 times the dose to be given).(30)

Acute zinc toxicity can occur at doses around 2 gm but doses of 150 mg daily for years have not produced toxicity.(31)

Molybdenum has not been reported to cause long-term toxicity in doses below 0.50 mg/day.(32)

Though unexpected, allergic reactions to fillers or coatings of vitamin pills could occur.

Barefoot doctors will be instructed in the signs and symptoms of potential adverse reactions to the pills. While no specific check-list will be systematically reviewed with participants at each monthly visit, patients will be asked to report any change in their general health status. If an allergic reaction or other potential drug effect is suspected, the pills will be stopped. Patients may be re-challenged in one month if the reaction was mild and reversible.

No provision is made for dose modification. Patients with persistent or recurrent toxicity suspected of being drug-related will not be given additional pills but will be followed for the duration of the trial for the outcomes of interest.

#### 6. Participant Compliance

For both the dysplasia and general population groups, compliance will be assessed in two ways: pill counts for all participants, and biochemical tests for a sample of them.

The barefoot doctors will distribute the monthly (28-day) pill packs. Each pill pack will be labelled with the participant's study ID number and name. Barefoot doctors will visit participants weekly for the first month of the study, then monthly thereafter. At the end of each month (28-day period), the barefoot doctor will collect the used pill pack and give out a new pack. A sample of the retrieved pill packs will be analyzed to assure us that the participant received the pills he was assigned to receive. Each month he will record in a log book the number of pills remaining for each subject. Logs of all contacts with the persons enrolled in the trial will also be maintained by the barefoot doctors. Bi-monthly sessions with participating barefoot doctors will be held to compile compliance statistics and to identify any practical problems that may arise.

Compliance will also be monitored using biochemical tests in a sub-sample of the participants. Approximately 400 randomly selected study subjects per year will be checked for compliance in each of the 5 years. Groups of 100 will be assessed at quarterly intervals. Each group of 100 will be composed of 20 dysplasia and 80 general population subjects. Compliance testing will be conducted as a part of the biochemical surveillance program (see 7 - Measures of Efficacy). In addition to measurements outlined there, erythrocyte glutathione reductase activation coefficients will be measured as an indicator of riboflavin status. Measuring riboflavin status is particularly appropriate as a check on compliance since dietary intake of riboflavin is depressed in over 90% of the Linxian population. Thus an adequate level is a good indicator that participants are taking pills. Compliance checks will be conducted without forewarn-

ing and records will be managed in such a way that results of these compliance checks may not be used to unblind the treatment group assignment for any subjects or study personnel.

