#### 4. Intervention Plan

The type and dosage of vitamins and minerals to be administered will differ for the two trials. For both trials, participants will receive various combinations of vitamin A, beta-carotene, riboflavin, niacin, vitamin C, vitamin E, selenium, zinc, and molybdenum, in doses between one and three times the U.S. Recommended Daily Allowances (RDA). The RDA for the nutrients with National Academy of Sciences-specified levels are:(27)

vitamin A - 5000 I.U., riboflavin - 1.6 mg, niacin - 18 mg,

vitamin C - 60 mg, vitamin E - 10 mg, and zinc - 15 mg.

Different study designs will be used for the two trials. The dysplasia trial will use a simple two-group design with one-half the patients assigned to receive multivitamin-multimineral pills to be taken daily. The other one-half participants will receive placebos identical in appearance to the active pills (see Table 5 for exact dosages).

For the general population trial, a factorial design will be used. The form of design to be used is a one-half replicate of a 2X4 factorial design.

The 4 proposed factors include:

A - vitamin A, beta-carotene, zinc

B - riboflavin, niacin

C - vitamin C, molybdenum

D - selenium, vitamin E

A full 4-factor factorial design would include  $2 \times 4 = 16$  different treatment groups (shown below).

|                |           |           |             |
|----------------|-----------|-----------|-------------|
| Placebo | A         | B         | AB   |
| C              | AC | BC | ABC         |
| D              | AD | BD | ABD         |
| CD      | ACD       | BCD       | ABCD |

One-half repetition includes only 8 treatment groups (the 8 underlined above).

This design was chosen because it will allow us to separate the main effects of various grouped factors (and certain of the interactions between factors) without requiring the excessive number of treatment groups needed for a 24 full factorial design or a factorial design evaluating greater numbers of factors. Further discussion of the rationale behind this choice of design is given in Appendix 3.

All treatment groups (including placebo) will have a small amount of thiamine (0.375 mg or 25% RDA) included. The addition of thiamin allows us to provide a small amount of a vitamin potentially useful for general health status, but which by itself would be unlikely to influence esophageal cancer incidence or mortality.

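### Riboflavin status says nothing about pill-taking in the half of each trial whose pills contain no riboflavin, and the protocol does not limit the check to the other half

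*Protocol*

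**What the plan says.** Section D.6 (Participant Compliance) measures compliance by pill counts in everyone and by biochemistry in a sample. On the sample: "Approximately 400 randomly selected study subjects per year will be checked for compliance in each of the 5 years". On its make-up: "Each group of 100 will be composed of 20 dysplasia and 80 general population subjects". Erythrocyte glutathione reductase is measured as the riboflavin indicator. The stated reason is that "dietary intake of riboflavin is depressed in over 90% of the Linxian population", from which the protocol concludes: "Thus an adequate level is a good indicator that participants are taking pills". No arm is excepted.

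Section D.4 (Intervention Plan) fixes who receives riboflavin. In the dysplasia trial it is "one-half the patients assigned to receive multivitamin-multimineral pills to be taken daily", and Table 5 lists riboflavin in that pill. For the rest: "The other one-half participants will receive placebos identical in appearance to the active pills". In the general population trial riboflavin sits in one factor only, "B - riboflavin, niacin". The eight groups used are placebo, AB, AC, BC, AD, BD, CD and ABCD.

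Three other places bear on the point:
- Section D.7 and Table 7 measure most of the other supplied nutrients in the same yearly sample.
- Section D.3 keeps the randomization key at NCI and blinds Linxian and Beijing.
- Section D.6 forbids using compliance results to unblind anyone.

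**The concern.** The reasoning suits the pilot (section C). There every participant took the same multivitamin, and mean urinary riboflavin rose from 756 before supplementation to between 1362 and 1423 during it (Table 4). The two trials differ: one is placebo-controlled and the other is factorial. A marker carried by half the pills can show pill-taking only in that half. Elsewhere a low level is expected whether or not pills are taken, and an adequate level points to diet or outside supplements.

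The pilot report itself concedes that a pill missing from the pack need not have been swallowed, and it turns to biochemistry for confirmation. After a null result, readers will ask whether the pills were taken, so the biochemical check must be interpretable. Staff in China run the assays but cannot tell B from non-B participants, and section D.6 gives no one the task of reading compliance by arm.

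**Working it through.** **Inputs from the protocol.** Four quarterly groups a year, each with 20 dysplasia and 80 general population subjects (D.6). Half the dysplasia patients are on active pills (D.4). Riboflavin is in AB, BC, BD and ABCD, that is 4 of 8 groups (D.4). Dietary riboflavin is depressed in over 90% (D.6).

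**Assumptions not in the protocol.** Arms are sampled in proportion to equal allocation. Dietary intake stands in for erythrocyte status, so background adequacy b lies between 0 and 0.10. The share s of riboflavin recipients who reach adequacy lies between 0.90 and 1.00.

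**1. The protocol's own figure.** 4 × (20 + 80) = 400 a year, as stated.

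**2. Who gets riboflavin, per 100 sampled.**
- Dysplasia: 20 × 1/2 = 10.
- General population: 80 × 4/8 = 40.
- With riboflavin: 50. Without: 50. Per year: 200 and 200.

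**3. Information in the riboflavin-free half.** The pills cannot change the level, so P(adequate | taking) = P(adequate | not taking) = b. The likelihood ratio is 1, and the result leaves any prior belief about pill-taking where it was.

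**4. Pooled reading, illustrated with 90% true pill-taking, b = 0.10, s = 1.**
- Adequate: 0.5 × (0.9 + 0.1 × 0.10) + 0.5 × 0.10 = 0.505.
- Taking and adequate: 0.5 × 0.9 + 0.5 × 0.9 × 0.10 = 0.495.
- P(taking | adequate) = 0.495 / 0.505 = 98%.
- Not taking and inadequate: 0.1 × 0.90 = 0.09. All inadequate: 1 − 0.505 = 0.495.
- P(not taking | inadequate) = 0.09 / 0.495 = 18%.

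The 98% is earned in the riboflavin half. In the other half P(taking | adequate) is just the assumed 90%.

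**5. Share adequate under perfect pill-taking, if pooled over arms:** 0.5 × s + 0.5 × b.

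| s | b = 0 | b = 0.10 |
|---|---|---|
| 1.00 | 50% | 55% |
| 0.90 | 45% | 50% |

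Read only in riboflavin arms, the same check would show s, that is 90-100%.

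**6. What else is measured in the riboflavin-free 50.**
- AC, AD and CD: 80 × 3/8 = 30. Each receives nutrients listed in Table 7 (A: retinol, carotenoids, zinc; C: ascorbic acid, molybdenum; D: tocopherol, selenium).
- Full placebo: 20 × 1/2 + 80 × 1/8 = 20. None of their pill content is in Table 7. Section D.4 puts a little thiamine in all groups including placebo, but thiamine is not among the Table 7 analytes.

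**7. Size of a factor-by-factor comparison.** Each of A, B, C and D is in 4 of the 8 groups. The yearly general population sample of 4 × 80 = 320 therefore gives about 160 assigned and 160 not assigned per factor. The dysplasia sample of 4 × 20 = 80 gives 40 and 40.

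**The case against.** The strongest reply is that the protocol states no compliance rule of the kind that would fail. It makes a one-way remark, that an adequate level suggests pills are being taken. It sets no threshold, does not equate a low level with missed pills, and defines no percentage pooled over arms. Step 4 shows that the one-way remark does well on average. Riboflavin is also an addition to a wider panel that section D.7 says is meant to assess compliance, and pill counts cover everyone. NCI holds the key, and section D.10 item 5 foresees monitoring nutritional status by treatment group. The ban on using compliance results to unblind suggests the authors knew that biochemistry tracks assignment. Finally, matching analytes to factors is normally left to an analysis plan, which is not at hand.

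Much of this stands. A reader might infer that the trial would report about 50-55% compliance even with perfect pill-taking. The protocol does not support that. It would require pooling, counting a low level as non-compliance, full response in every recipient, and dietary intake as a proxy for status, and none of these is stated. Nor do factors A, C and D go unchecked, since other analytes serve them.

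The reply does not rescue the sentence itself. It is written for participants in general, and in half of them even the stated direction carries no information. The by-group wording in D.10 item 5 belongs to part (a), secular and seasonal surveillance; part (b), compliance testing, does not carry it. The point rests on an inference the protocol does state, not on a detail it leaves out.

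**Conclusion.** The concern holds in a limited form. By the protocol's own design, riboflavin status is uninformative about pill-taking in about 200 of the 400 people checked each year, and section D.6 recommends it without saying so. That count needs only proportional sampling of arms. Of each 50 riboflavin-free subjects, 30 receive another measured nutrient, provided those analytes respond to the pills; the other 20 have pill counts only.

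The 45-55% range is a warning about one possible misreading, conditional on pooling and on reading a low level as non-compliance. It is not a forecast of what the trial will report. Nothing in the primary mortality analysis depends on the riboflavin result. What is at stake is how compliance is interpreted, above all if the trials show no effect.

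**What to change.** Amend section D.6 in four respects:

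1. Limit the riboflavin statement to the factor B groups (AB, BC, BD, ABCD) and the active dysplasia arm.
2. Have NCI, which holds the key, score biochemical compliance by assigned factor from the existing Table 7 analytes, comparing assigned with not assigned: A by retinol, carotenoids and zinc; B by glutathione reductase activity; C by ascorbic acid and molybdenum; D by tocopherol and selenium. Scoring there keeps staff in Linxian and Beijing blind.
3. Use the non-assigned groups to detect outside supplement use, since regular vitamin use is an exclusion at entry (section D.1).
4. State that compliance in full-placebo participants, in both trials, rests on pill counts alone.

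No new samples or assays are needed. The cost is a little more analysis work at NCI.

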## 7. Measures of Efficacy

Esophageal cancer mortality over a 4 1/2-year period beginning 6 months after the start of the nutritional supplementation will be the primary outcome variable to be measured in the dysplasia trial and the population trial. Total mortality, total cancer mortality, and esophageal and total cancer incidence will also be assessed. Several ancillary assessments will also be made. These include: 1) reviewing cytologic regression and/or progression in all patients in the dysplasia trial, 2) doing DNA content analysis on a sample of these cytologic slides, 3) endoscopying a sample of 200 dysplasia patients before starting pills and again after 18 months of pill-taking to assess histologic changes and correlate the histology and cytology findings, and 4) obtaining 24-hour urine collections before and after the start of pill-taking to evaluate the effect of vitamin C on nitrosamine formation. (See Appendix 3 for more details on these ancillary assessments).

During the course of the study barefoot doctors will identify all deaths to study subjects. Information from medical records will be abstracted to include date and cause of each death. Incident cancer cases will also be identified. Date of diagnosis and type of cancer will be determined. Annually, in collaboration with NCI, the CI will calculate age- and sex-specific rates of mortality from all causes and rates of mortality and incidence from esophageal and all other cancers among study participants, stratified by treatment group (with the code identifying placebo and treatment groups broken only if there are highly significant differences).

A biochemical surveillance program will be included in both trials to provide information on background of nutrients for trial participants before the interventions, to assess compliance, and to allow us to measure seasonal and secular variation during the interventions. To accomplish this, all patients participating in the dysplasia trial and a sample (approximately 10%) from the general population trial will be asked to provide samples of blood, urine, hair, and nails prior to the onset of pill-taking.

During the interventions, 400 study subjects per year will be selected at random to have blood and urine collected and have a dietary history and anthropometric measurements taken. Blood will be analyzed for the various vitamins and minerals being administered during the trials and urine will be analyzed for nitrosamines (see Table 7 below). This surveillance will include participants from both trials limited to those who had samples collected before the onset of pill-taking and will be performed throughout the year (100 persons every 3 months; 20 from dysplasia trial, 80 from general population trial).

The laboratory analyses for this surveillance program will be performed in China with a 10% sample being sent to the U.S. for simultaneous analysis as a part of an ongoing quality control program.

In addition to assessing compliance and seasonal/secular changes, baseline measurement of nutrients in all dysplasia trial participants will allow us to adjust for any non-random differences between treatment groups and review our outcomes by baseline nutrient status.

Table 7

Laboratory analyses to be conducted during the trials.

| Analyte | Tissue               | Method                             |
|----------------|-----------------------------|-------------------------------------------|
| Retinol        | Plasma                      | HPLC                                      |
| Carotenoids    | Plasma                      | HPLC                                      |
| Tocopherol     | Plasma                      | HPLC                                      |
| Riboflavin     | Erythrocytes                | Glutathione reductase
activity         |
| Niacin         | Urine                       | Spectrophotometric                        |
| Ascorbic acid  | Plasma                      | Spectrophotometric                        |
| Molybdenum     | Erythrocyte,
hair, nails | Spectrophotometric                        |
| Selenium       | Erythrocyte,
hair, nails | Spectrophotometric,
neutron activation |
| Zinc           | Plasma, hair                | Spectrophotometric                        |
| Cholesterol    | Plasma                      | Spectrophotometric                        |

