#### (c.) Data Analysis

The methods of analysis to be applied to the data collected during these trials include simple contingency table analysis and Cox's method of regression analysis for survival data.(34) The use of regression methods will allow for incorporation of variables stratified on at randomization and adjustment for risk factors which are found by the initial interview to be nonrandomly distributed between treatment groups.

Analysis of the dysplasia trial data will allow us to make a statement about the effect of the combined multivitamin-multimineral preparation only, while in the general population trial we will be able to separate out the effects of the several factors.

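### Ancillary assessment 4 names an effect of vitamin C on nitrosamines, but no arm in either trial separates vitamin C from molybdenum

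*Protocol*

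**What the plan says.** Section D.7 (Measures of Efficacy) lists four ancillary assessments. The fourth is "obtaining 24-hour urine collections before and after the start of pill-taking to evaluate the effect of vitamin C on nitrosamine formation". The item names no trial, arms, number of participants or comparison, and refers to Appendix 3 for details. In the document at hand that appendix is only a pointer to other material.

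Section D.4 (Intervention Plan) defines the third factor of the general population trial as "C - vitamin C, molybdenum". For the other trial it says "The dysplasia trial will use a simple two-group design with one-half the patients assigned to receive multivitamin-multimineral pills to be taken daily", and "The other one-half participants will receive placebos identical in appearance to the active pills". Table 5 lists nine nutrients for the dysplasia preparation, vitamin C and molybdenum among them.

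Section D.9(c) (Data Analysis) says that the dysplasia data will allow the investigators to "make a statement about the effect of the combined multivitamin-multimineral preparation only".

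Two further statements in section D.7 bear on the point. The biochemical surveillance programme is meant in part "to allow us to measure seasonal and secular variation during the interventions". For its samples, "urine will be analyzed for nitrosamines (see Table 7 below".

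**The concern.** The objective credits one nutrient with an effect that the design can assign only to a pair of nutrients or to a nine-nutrient preparation. If urinary nitrosamines differed between groups, a report that followed the stated objective would call this a vitamin C effect, although molybdenum, or in the dysplasia trial any of the other eight nutrients, was given to exactly the same people.

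A second issue is what the objective leaves open. The only contrast visible in the item is between two collection times. Section B names foods as a source of nitrosamines, and section D.7 sets out to measure seasonal variation. Pre-pill samples would fall within limited recruitment periods. Section D.3 gives about one month for identification plus two for enrolment in the dysplasia trial, and 2-3 months for evaluation plus four for accrual in the general population trial. If someone analysed only the change within treated persons, season would be mixed with treatment.

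**Working it through.** The plan gives no figure on this point, so there is none to reproduce. The check is of design structure.

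**Inputs.** The eight underlined arms and the four factors come from section D.4, the dysplasia preparation from Table 5, and the general population doses from Table 6.

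**Step 1: vitamin C and molybdenum by arm, general population trial.**

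| Arm | Vitamin C | Molybdenum |
|---|---|---|
| Placebo | no | no |
| AB | no | no |
| AD | no | no |
| BD | no | no |
| AC | yes | yes |
| BC | yes | yes |
| CD | yes | yes |
| ABCD | yes | yes |

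The two columns are identical. In a model with separate terms b(vitC)·x(vitC) + b(Mo)·x(Mo), x(vitC) = x(Mo) in every arm. Only the joint effect of the pair can be estimated: b(vitC) + b(Mo), plus any interaction between them. Arms that isolate vitamin C: 0 of 8.

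**Step 2: dysplasia trial.** The active arm receives all nine nutrients and the placebo arm none of them, so nine indicator columns coincide and only their joint effect can be estimated. Arms that isolate vitamin C: 0 of 2.

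**Step 3: can the two trials together separate them?** Vitamin C is 120 mg in Table 6 and 180 mg in Table 5, with molybdenum at 30 mcg in both. A comparison across the trials is not randomised, however. The populations differ, and so do the doses of vitamin A, riboflavin and zinc. It does not rescue the claim.

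**Step 4: what the factorial does identify.** Every arm holds an even number of factors, so the defining relation is I = ABCD. Multiplying by C gives C = ABD: the main effect of factor C is aliased only with the three-factor interaction ABD. The randomised contrast is

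mean(AC, BC, CD, ABCD) − mean(placebo, AB, AD, BD).

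On each side A appears in 2 of 4 arms, B in 2 of 4 and D in 2 of 4. Factor C is therefore orthogonal to A, B and D, and its effect as a pair can be separated from theirs.

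**Step 5: season.** Let s be a shift between the two collection times that all groups share, and d the effect of the randomised factor.

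- Change in the group with the factor: s + d.
- Change in the group without it: s.
- Difference between the groups: (s + d) − s = d.

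A within-person change in treated participants alone would estimate s + d. A comparison between randomised groups sampled over the same calendar period estimates d. The protocol gives no value for s, so no size can be put on the risk.

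**Step 6: Table 7.** The text cites this table for urinary nitrosamines. It has ten rows, none for nitrosamines, and its only urine row is niacin.

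**The case against.** The strongest reply on attribution is that the wording merely names the hypothesised agent. Section B credits only vitamin C with blocking nitrosamine formation, section D.4 says openly that the design separates grouped factors, and section D.9(c) already restricts the dysplasia conclusions. This lowers the stakes but does not answer the point. A prior belief about mechanism does not identify an effect. Section B also reports that molybdenum inhibited forestomach cancers in rats, so the protocol does not treat the companion nutrient as inert. The reply does hold on one matter: in a factor-C contrast within the general population trial the ambiguity is confined to molybdenum, because A, B and D balance out.

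A reader might go further and infer that the protocol plans an uncontrolled before/after analysis and so confounds treatment with season. The documents do not support that. The phrase gives the times of collection and does not say how the samples will be compared. A pre-pill sample is also what a baseline-adjusted randomised comparison needs. Both trials are individually randomised with a concurrent placebo group. Surveillance sampling is spread over the year, and section D.10 (item 5) speaks of monitoring seasonal change in nutrition and diet across treatment groups as well as within them. Details may stand in the appendix or in an analysis plan, neither of which is shown, so their absence is not a finding.

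Nor does the gap in Table 7 show that no nitrosamine assay is planned. The text states the assay, and the table belongs to the surveillance programme. The gap is an editorial inconsistency.

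**Conclusion.** The attribution point holds. None of the ten arms across the two trials (8 + 2) isolates vitamin C, and because this follows from the composition of the pills, no appendix or analysis plan could repair it. The general population trial can support a statement on vitamin C plus molybdenum, subject to the alias with ABD. The dysplasia trial can support one on the nine-nutrient preparation.

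Seasonal confounding is a possibility that the present wording leaves open, not an error that has been shown. Its removal by a between-group comparison rests on two assumptions: urine is collected from both randomised groups over the same calendar period, and the seasonal shift is common to them.

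Severity is minor. The conclusion that may be drawn from one ancillary assessment changes, and nothing else in the trial does.

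**What to change.** 1. Reword ancillary assessment 4 in section D.7 so that its target is the effect of factor C (vitamin C plus molybdenum) if it is done in the general population trial, or of the whole preparation if it is done in the dysplasia trial. Say which trial and which arms are sampled.
2. State the comparison: on-treatment urinary nitrosamines between randomised groups (the four arms with factor C against the four without, or active against placebo), with urine collected over the same calendar period and adjustment for the pre-pill value.
3. Add a urinary nitrosamine row, with its method, to Table 7, or correct the cross-reference.

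The cost is wording and analysis specification, with collections needed from both randomised groups. What is given up is the claim about vitamin C alone, which the design cannot support. The primary outcome, sample size and alpha stay as they are.
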